**Secondary outcome measures: clinical effectiveness of the intervention (observational comparison)**	
**Change in healthy lifestyles and cardiovascular risk factors** of high risk patients exposed to the intervention programme 12 months after exposure	
• Adherence to recommendations on physical activity and healthy diet:	
i) % who meet the recommended level of physical activity (150 min/week of moderate physical activity or 75 min/week of intense physical activity) , among those who did not meet it at recruitment;	Baseline and 12 months after programme exposure
ii) % who meet the recommended level of fruit and vegetable intake (5 portions/day), among those who did not meet it at recruitment. •Changes in physical activity (minutes of moderate to vigorous physical activity) or in fruit and vegetable intake	
• % whose BMI decreases by 5% by 12 months after the intervention • potential effects of the preventative intervention on other cardiovascular factors including cholesterol and triglyceride levels, as well as BMI and blood glucose (data derived from the annual clinical follow-up)	Electronical Health Record

Bolded text refers to the outcome dimensions composed of multiple indicators

Underlined text refers to possible T2D risk screening strategies to be adopted by centres

Patients exposed to the intensive intervention for the promotion of healthy lifestyles (i.e. the prescription of lifestyle change) in each centre/group will be followed-up every year in the centre with measurement of clinical parameters and the assessment of physical activity and diet with the *Prescribe Vida Saludable* (Prescribe Healthy Lifestyle) questionnaires [43], incorporated in the electronic health record (Table 2).3.Associated factors

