#### Analysis

All the analyses will be carried out on an intention-to-treat basis and then exploratory analysis will be performed by protocol and subgroup. We will estimate the absolute and relative pre-post intra-centre and between groups differences and the 95% confidence intervals using multi-level logistic regression for dichotomous variables (e.g. proportion of patients with a prescription for lifestyle change). As the sample size for evaluating the implementation objectives is over 20,000 patients, all the comparisons will be significant from a statistical point of view, and hence, emphasis will be placed on the magnitude of these differences, following the Cohen categories based on standardised differences: < 0.5; ≥ 0.5 to ≤ 0.8 and > 0.8 being considered to indicate small, moderate and large effects respectively. Comparisons will be adjusted for potential confounding factors, through stratified analysis and the inclusion of such factors in the regression models following forward and backward strategies guided by the stratified analyses.

To assess the maintenance of implementation outcomes through the 24-month follow-up, mixed-effect generalised longitudinal models will be built with fixed effects (intervention group, effect of time on monthly process indicators and interaction time-intervention) and random effects on the intercept and the slope (for each subject, doctor-centre). Said models will be adjusted for the potential confounding variables, following a forward strategy guided by the stratified analyses. Through these statistical models, we will take into account the intra-class correlation (between doctor-centre) and the hierarchical nature of data: patients nested by medical consultations and these grouped by health centre. All the analyses were carried out using SAS statistical software.

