Regarding the secondary outcome variables, the percentages (e.g. % of patients who meet recommendations on physical activity) were compared using chi-square or non-parametric tests. Quantitative variables were compared using t-tests (comparison of the means). For these outcome measures, pre-post differences and differences between study groups will be estimated, and 95% confidence intervals (CIs) will be calculated on an intention-to-treat basis. Stratified analysis will be performed, mixed-effects generalised models will be built to estimate the differences between the groups adjusted for factors that confound or moderate the effect of the intervention (baseline demographic and clinical characteristics) and adjusted differences, adjusted odds ratios (ORs) and 95% CIs will be calculated at the patient level, taking into account the hierarchical and multicentre structure of data. To explore a potential modifying effect of the intervention on clinical outcomes obtained attributable to the procedure for creating the interprofessional community of practice, we will conduct comparisons by intervention protocol between groups using matching by propensity scores calculated on the basis of the characteristics of patients recorded in their health record. This will permit us to analyse the association between the actual intervention dose received (assessment of lifestyle habits, assessment of habits plus advice, and assessment of habits plus advice plus prescription) and the event of interest (change in lifestyle habits or weight loss) as a function of one or other engagement procedure, pairing patients participating in one or another comparison group in a 1:1 ratio on the basis of them having a similar probability of having received said treatment or intervention dose.

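### Continuous secondary outcomes: the patient's own baseline value is collected but not fixed as a covariate, which costs precision and can leave baseline differences in the between-arm estimate

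*Protocol article*

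**What the plan says.** The Analysis section of the protocol article treats the secondary outcomes in two layers.

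- **Unadjusted layer.** Percentages "were compared using chi-square or non-parametric tests". "Quantitative variables were compared using t-tests (comparison of the means"). For these outcomes, "pre-post differences and differences between study groups will be estimated, and 95% confidence intervals (CIs) will be calculated".
- **Adjusted layer.** After stratified analysis, mixed-effects models estimate the group differences, "adjusted for factors that confound or moderate the effect of the intervention (baseline demographic and clinical characteristics"). A propensity-matched exploratory comparison by intervention dose follows.

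Table 2 lists the secondary outcomes as an observational comparison in exposed high-risk patients, measured at baseline and 12 months after exposure. One entry is "Changes in physical activity (minutes of moderate to vigorous physical activity) or in fruit and vegetable intake". BMI, cholesterol, triglycerides and glucose come from annual follow-up. The binary activity and diet outcomes count patients reaching the target "among those who did not meet it at recruitment", and the binary BMI outcome is a 5% fall.

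The text neither names the outcome's own baseline value as a model term nor says that it is left out.

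**The concern.** For a continuous outcome measured twice, the baseline value is usually the strongest available predictor of the 12-month value. It belongs in the model for precision, whether or not it appears to confound. The stated rule admits covariates because they confound or moderate, and a baseline that looks balanced between arms could fail that rule and take its precision with it.

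The unadjusted comparisons do not condition on baseline at all. If the arms differ at baseline by chance by d, and r is the baseline-to-12-month correlation, a comparison of 12-month means carries r × d and a comparison of changes carries −(1 − r) × d. With only nine centres, d need not be small.

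Activity minutes and fruit and vegetable intake are the most exposed. They are behaviours, and it is not clear that the bracket about demographic and clinical characteristics includes them. At stake is the precision, and to a lesser degree the accuracy, of the between-arm estimates for lifestyle and risk factors.

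**Working it through.** The plan gives no precision figure for continuous secondary outcomes, so there is none to reproduce. Its secondary sample size concerns a proportion (5% weight loss) and uses no baseline correlation. Only its patient number is taken here.

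**Inputs**
- Centres: 5 sequential, 4 global (Random allocation).
- ICC 0.03, 308 patients per group, 10% loss (Sample size): 308 × 0.9 = 277 analysed per arm.
- r, the baseline-to-12-month correlation: not in the document. Assumed 0.5 to 0.9.

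**1. Chance baseline difference between arms, in outcome SDs**
- Between-centre part: 0.03 × (1/5 + 1/4) = 0.0135.
- Within-centre part: 0.97 × 2/277 = 0.0070.
- SD = √(0.0135 + 0.0070) = √0.0205 = 0.143; 95% range ±1.96 × 0.143 = ±0.28.
- With 340 per arm (the main-outcome figure, 425 × 0.8) the SD is 0.139, so the choice hardly matters.

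**2. Amount carried into an estimate without baseline, for a one-SD difference (0.143)**

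| r | 12-month means, r × 0.143 | changes, (1 − r) × 0.143, opposite sign |
|---|---|---|
| 0.5 | 0.072 | 0.072 |
| 0.7 | 0.100 | 0.043 |
| 0.9 | 0.129 | 0.014 |

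**3. Variance relative to a comparison of 12-month means (= 1), same r within and between centres**

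Change score: 2(1 − r). Baseline-adjusted: 1 − r². Their ratio is (1 + r)/2.

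| r | change | adjusted | cut against change | cut against means |
|---|---|---|---|---|
| 0.5 | 1.00 | 0.75 | 25% | 25% |
| 0.7 | 0.60 | 0.51 | 15% | 49% |
| 0.9 | 0.20 | 0.19 | 5% | 81% |

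**4. If centre effects at the two times are uncorrelated**

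The between-centre share of the variance is 0.0135/0.0205 = 0.66, and the within-centre share is 0.34.
- If the centre-level slope is estimated separately, only the within part gains. The cut against means is 0.34 × r², which is 8.5% at r = 0.5 and 28% at r = 0.9.
- With one patient-level slope of about r, the relative variance is 0.66(1 + r²) + 0.34(1 − r²): 1.08 at r = 0.5, 1.16 at 0.7 and 1.26 at 0.9. The gain against means is then lost.
- The change score has 0.66 × 2 + 0.34 × 2(1 − r): 1.66, 1.52 and 1.39, so it remains worse than either.
- The single-slope model breaks even with means once the centre-level correlation reaches about 0.12 (r = 0.5) to 0.22 (r = 0.9). This solves 0.66(1 + r² − 2r × r_c) + 0.34(1 − r²) = 1 for the centre-level correlation r_c.

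The same centres are measured 12 months apart, so a correlation near zero is an extreme case.

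**The case against.** **The bracket may be the adjustment set.** A reader might infer that baseline enters only if a test finds it to confound or moderate. The text does not say so. The bracket can equally mean that baseline demographic and clinical characteristics are the covariates, and baseline BMI, lipids and glucose would fit that naturally. The stepwise rule, "following forward and backward strategies guided by the stratified analyses", is stated for the main outcomes, not these. This stands. What remains is that no wording commits to the own-baseline value, and activity and diet are the doubtful cases.

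**An imbalanced, prognostic baseline is a confounder and qualifies under the plan's own rule.** A reader might conclude that imbalance stays in every estimate. It does in the t-tests and change comparisons. In the adjusted models it stays only if selection misses it. The precision argument is untouched, because a balanced baseline can still be dropped.

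**The exact covariate list is for the analysis plan.** True of the full list. The point here concerns the stated rule for admitting covariates and the stated unadjusted tests.

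**The binary outcomes escape.** Correct. Those for activity and diet already condition on status at recruitment, and the BMI outcome is defined against the patient's own baseline.

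**The comparison is labelled observational.** Patients are exposed after centres are allocated, so baseline differences may be systematic. The formulas for r × d and (1 − r) × d assume chance differences. With systematic ones, baseline adjustment and change scores answer different questions and neither is right by default. This stands, and it is why a change-score sensitivity analysis is needed.

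**Conclusion.** The concern holds for the continuous secondary outcomes only. The t-tests and change comparisons lose precision and carry baseline differences with an SD of about 0.14 outcome SD. The adjusted models may do so if the baseline is left out. The gain from fixing the baseline is modest against change scores (25% of variance at r = 0.5, 5% at r = 0.9) and larger against raw means (25% to 81%). The latter depends on centre effects persisting over the year.

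These sizes rest on the plan's ICC of 0.03 applied to the continuous outcomes and on an assumed r. The document does not support the stronger readings that baseline is admitted only after a test, or that all secondary estimates are left imbalanced. Severity is low: secondary outcomes, in a comparison labelled observational.

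**What to change.** For each continuous secondary outcome, state that the main between-arm estimate comes from a mixed model of the 12-month value with arm, a centre random effect and the patient's baseline value of that outcome. The baseline term is included whatever any confounder or moderator screen shows. Keep the t-tests as descriptive only.

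Report the change-score result as a sensitivity analysis. The centre mean of the baseline should not be mandatory. With nine centres it takes centre-level degrees of freedom from 7 to 6 (critical t from 2.365 to 2.447). It is reasonable as a second sensitivity analysis, since it covers the case in step 4 where centre effects do not persist.

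The cost is a sentence or two in the analysis text and one or two extra model fits. Table 2 already schedules the baseline values, so no new data are needed.

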## Discussion

The present implementation research project is framed in the context of the translation of practices with proven effectiveness for the prevention of T2D. This disease is one of the main causes of illness and premature death in most countries, and hence, it has become a priority public health issue worldwide. There is an extensive evidence concerning interventions that succeed in reducing the risk of developing T2D, but there is also evidence of the gap between what it is known to be effective and what is actually being done in our health system. Yet, the implementation scientific objective is to evaluate the effect of different procedures for engaging PHC professionals in the creation of an interprofessional community of practice for the collaborative modelling and integration of a T2D primary prevention recommended clinical practice.

In a broader sense, the project seeks to integrate a T2D prevention programme, based on scientific evidence and recommended care, into the portfolio of services of PHC centres in a feasible and sustainable way, ensuring that it is as efficient as it should be, has a wide coverage and is effective among the users that could potentially benefit from it, thereby resulting in improvements in care practice, reducing the delivery of services that do not provide clinical benefits, increasing quality and improving health outcomes, through the efficient and sustainable use of health system resources. Further, the project seeks to optimise and transform clinical practice and its organisation, refocusing it towards an approach that enables feasible, sustainable and effective translation of interventions with proven efficacy, and thereby, improve the provision services by our health professionals. By incorporating and evaluating new strategies or organisational models in health centres, specifically the creation of interprofessional communities of practice, focused on collaborative planning and the redefining of professional roles, sharing out of tasks, and optimisation of the provision of care and services, will enable us to advance our knowledge of how to integrate interventions and therapies that have proven effective but are not being widely used into daily practice in sustained and continuous manner. If the findings are positive, this research will provide health planners and research community with evidence supporting the view that there is a need to introduce and assess this type of implementation strategies to enhance the adoption of new practices and innovations in operative procedures, strategies and resources, as a means to achieve integration of interventions with proven efficacy in clinical practice and in the PHC portfolio of services, and that they really reach the users who have a need for them.

However, several threats and limitations could be advanced. First, the limited number of centres in study may affect the generalizability of the study results. Second, to assure the binomial of “fidelity” in the application of the strategy and the necessary “adaptability” to the local context of each centre will be both a big challenge and an issue of scientific relevance. And third, the time necessary for the achievement of relevant changes in clinical practice is certainly unknown and also warrants careful considerations in the interpretation of study results. Additionally, low interest or lack of motivation of patients to improve their health, due to their condition of being at risk and not having a disease, may affect actual intended reach of the programmes implemented in centres. At the collaborating centre’s level, two major threats could be envisaged, being these maintaining the commitment and involvement of professionals throughout the project, and the rotation in or movement from centres of personnel. And lastly, at the organisational level, lack of support from the Directorate in the provision of resources that guarantee the correct execution of the project, and the competition with other initiatives and projects to be carried out in the organisation, may undermine implementation results.

## Abbreviations

ACG: Adjusted Clinical Groups
BMI: Body mass index
CFIR: Consolidated Framework for Implementation Research
CI: Confidence intervals
HbA1c: Haemoglobin A1c or glycated haemoglobin
ICC: Intra-class correlation coefficient
ILS: Implementation Leadership Scale
OR: Odds ratio
OR4KT: Organizational Readiness for Knowledge Translation
PHC: Primary health care
T2D: Type 2 diabetes
TDF: Theoretical Domains Framework
